### Interventions

The interventions will be delivered within 10 working days of randomisation by experienced physiotherapists, trained in acupuncture to at least the minimum standard for basic membership of the Acupuncture Association of Chartered Physiotherapists (AACP) (35 hrs of training). The participant's GP will be contacted at the time of randomisation and asked to avoid co-interventions for the period of the trial wherever possible, but especially until the 6-week follow up has been completed. However, if the GP feels that symptoms are sufficiently troublesome to need further treatment this will be at the GPs discretion. Information about co-interventions will be collected in the follow-up questionnaires and by review of a sample of participants' clinical records.

#### a) Advice and exercise

Advice will be supplemented by a leaflet based on the **arc **Knee OA publication. This leaflet contains standard advice on the use of analgesia. If already using non-steroidal anti-inflammatory drugs, participants will be permitted to continue their stable dose. Participants will have the opportunity to discuss elements of the advice leaflet and exercise programme with their physiotherapist. In line with current practice, a maximum of 6 × 30-minute treatment sessions will be given over a period of 6 weeks. The advice and exercise programme has been developed through the use of reviews of current best evidence [23,27,55], clinical guidelines [9], a survey of current physiotherapy practice for knee pain [56], consensus workshop, and local physiotherapy practice.

The exercise programme will include concentric, eccentric, isometric and balance exercises. Specificity of training, particularly in the first 6 weeks, is important and therapists will aim for a mix of functional exercises, open & closed kinetic chain exercises and accelerated walking elements. They will also clearly identify a home exercise programme with set targets. The intensity of the exercises will be progressively increased at each session. Previously sedentary individuals who are relatively untrained will initially be prescribed exercise of a low intensity (eg. 1–3 sets of 8–12 repetitions of an exercise, 2–3 times per week). Progression to medium and high intensity exercise will occur only once adaptation to the current level of training has occurred.

Exercises will be prescribed and individualised for each participant by the treating physiotherapist from "Physio Tools" , a frequently used software package in physiotherapy. Hydrotherapy, group-based work, electrotherapy, additional acupuncture outside of the protocol and intra-articular injections will not be permitted. Participants may receive advice on the use of walking aids, and hot and cold applications. The key messages within the advice to participants include the common nature of knee problems and that rest for more than a day or two usually does more harm than good.

#### b) Advice and exercise plus true acupuncture

In addition to advice and exercise as detailed above, participants randomised to this group will receive 6 × 30-minute treatments of acupuncture, delivered over a period of 3 weeks. The acupuncture protocol is based on the concept of "treatment adequacy" which has been introduced by Ezzo et al [46] and Melchart et al [57] and has been shown recently to affect long term clinical outcome [58]. Physiotherapists delivering the treatment are provided with a choice of a total of 16 most commonly cited local and distal points from which they are required to chose between 6 – 10 points for each session. Local points available include: Sp 9, Sp 10, St 34, St 35, St 36, Xiyan, Gb 34 and trigger points. Distal points available include: LI 4, TH 5, Sp 6, Liv 3, St 44, Ki 3, BI 60 and Gb 41.

Treatment will be performed with sterilised disposable steel needles, 30 × 0.3 mm. The depth of the needle insertion should be between 0.5 – 2.5 cm depending on the points selected for treatment and the needles will be manipulated until de-qi sensation is achieved. Therapists allow 25 (min) to 35 (max) minutes between insertion of the last needle and cessation of treatment and during that time they are to revisit the needles as appropriate. If the sensation is maintained, they should manipulate each needle lightly, if the de-qi sensation is no longer there, they use stronger manipulation in order to elicit it.

Participants will be informed that they may or may not experience an aching, warm or `tingling' sensation from this type of stimulation. Therapists question participants at each session to ask them to describe the sensation they feel on needling, which is then recorded on a standard proforma. This also collects information on attendance, failed appointments, physiotherapist's diagnosis and whether any additional treatment modalities or specialist referrals are made.

#### c) Advice and exercise plus placebo acupuncture

In addition to advice and exercise as detailed above, participants randomised to this group will receive sham acupuncture which involves the placement of mock needles [47] upon a pre-defined set of points. The mock needle is a new device, which participants find indistinguishable from true acupuncture and has been used with success in a randomised trial comparing the effects of true versus placebo acupuncture in the treatment of shoulder pain [59]. The mock needle operates by allowing the shaft of the needle to collapse in the handle, creating an illusion of insertion (Figure 1 – adapted from [47])

The points chosen for the sham intervention receive no stimulation and participants will be told, as for the true acupuncture group, that they may or may not experience any particular sensation from this type of stimulation. The same parameters as for true acupuncture apply: placement of a minimum of 6 needles, and 6 × 30 minutes sessions within 3 weeks, with monitoring of elicited sensations.

### Audit of interventions

Using a standard proforma, the physiotherapists record the number and duration of treatment sessions each participant receives, plus details about the advice and exercises prescribed, the location and number of acupuncture points (where applicable) and any adverse reactions. The sensation that needling (true or placebo) evokes has been shown to be a significant correlate of acupuncture-induced analgesia (this has been a finding from both clinical and experimental studies). Hence, the sensation evoked from each treatment in the acupuncture groups will also be recorded. Acceptability and credibility of the interventions will be evaluated using a telephone follow-up at 2 weeks from the beginning of treatment and a questionnaire administered at 6 weeks [60].

### Baseline measures

Participants who give verbal consent to participate in the trial are posted a baseline questionnaire which they are asked to complete and bring with them to the research interview and examination. Information collected on this questionnaire is detailed in Table 2. These variables will be used to describe the study sample and as baseline measures of outcomes. Immediately following written informed consent, participants undergo a research interview and examination which follows a previously published schedule [66].

### Follow-up

Outcome measures will be performed at 2 weeks (Table 3), 6 weeks, 6 months and 12 months (Table 4). Follow-up assessments will be performed using a telephone call at 2 weeks after the first treatment and self-completed postal questionnaires at all other time points. Non-responders will be telephoned 2 weeks after mailing the follow-up questionnaire on up to 2 occasions and posted a replacement questionnaire with a reminder letter if there is still no response at 4 weeks.

### Sample size calculation

The primary outcome measure for this trial is the Western Ontario and McMaster Universities Osteoarthritis Index (WOMAC) pain sub-scale [61]. We have defined overall success as a 20% difference in the WOMAC pain sub-scale between true acupuncture and advice and exercise alone at 6 months. For this comparison, a minimum of 90 participants is needed in each group to reject the null hypothesis with 80% power and at a 5% significance level (two-tailed) [68]. As our trial will compare sham acupuncture with advice and exercise alone we have three groups and so need 270 participants. Allowing for a 30% drop out rate in those recruited to the trial, the total number of participants required to be randomised is 350.

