**Methods/Design:**

This randomised clinical trial will recruit 350 participants with knee pain to three intervention arms. It is based in 43 community physiotherapy departments in 21 NHS Trusts in the West Midlands and Cheshire regions in England. Patients aged 50 years and over with knee pain will be recruited. Outcome data will be collected by self-complete questionnaires before randomisation, and 6 weeks, 6 months and 12 months after randomisation and by telephone interview 2 weeks after treatment commences. The questionnaires collect demographic details as well as information on knee-related pain, movement and function, pain intensity and affect, main functional problem, illness perceptions, self-efficacy, treatment preference and expectations, general health and quality of life. Participants are randomised to receive a package of advice and exercise; or this package plus real acupuncture; or this package plus sham acupuncture. Treatment details are being collected on a standard proforma. Interventions are delivered by experienced physiotherapists who have all received training in acupuncture to recognised national standards. The primary analysis will investigate the main treatment effects of real or sham acupuncture as an adjunct to advice and exercise.

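### The 350 to be randomised does not cover the stated 30% drop-out: it covers about 23%, and at 30% loss power is about 76%, not 80%

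*Protocol article*

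**What the plan says.** The Sample size calculation section of the protocol article takes WOMAC pain as the primary outcome and sizes the trial for "a 20% difference in the WOMAC pain sub-scale between true acupuncture and advice and exercise alone at 6 months". For that comparison it states that "a minimum of 90 participants is needed in each group to reject the null hypothesis with 80% power", with a two-sided 5% test. It then extends the number to all arms: "we have three groups and so need 270 participants". The last step is the drop-out allowance: "Allowing for a 30% drop out rate in those recruited to the trial, the total number of participants required to be randomised is 350".

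The Abstract (Methods/Design) gives the same figure as the recruitment target: "This randomised clinical trial will recruit 350 participants with knee pain to three intervention arms". The Randomisation section sets allocation at 1:1:1.

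**The concern.** The allowance is expressed as a share of the people recruited. The number left for analysis is therefore the number recruited times 0.70, and that product should be at least 270. With 350 it is not.

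This matters because the paragraph is the article's justification for the size of the trial. A reader would take it to mean that the 6-month primary comparison keeps 80% power even if 30% of participants are lost. If the allowed-for loss occurs, that is not so. The Analysis section plans no interim look at the outcomes and the Sample size calculation section mentions no sample size review, so nothing in the article would bring the shortfall to light during the trial.

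**Working it through.** **Inputs**, from the Sample size calculation section unless noted:

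- analysable participants: 90 per group, 270 in three groups
- power 80%, two-sided 5% test
- drop-out: 30% of those recruited
- number to be randomised: 350
- allocation: 1:1:1 (Randomisation section)

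**1. Reproducing the printed figure.** Multiplying the analysable number by (1 + drop-out) gives 270 × 1.30 = 351, which matches 350 to rounding. Dividing by (1 − drop-out) gives 270 / 0.70 = 385.7, so 386, which does not match. The article does not show its formula, so the first form is an inference, but it is the one that reproduces the figure.

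**2. Number consistent with 30% loss.** 386 in total. Worked per arm, 90 / 0.70 = 128.6, so 129 per arm, or 387 with equal arms. The printed figure is 36 to 37 short; 36/386 is about 9%.

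**3. What 350 leaves after 30% loss.** 350 × 0.70 = 245, and 245 / 3 = 81.7 per arm, against a stated minimum of 90.

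**4. Loss that 350 does cover.** 1 − 270/350 = 80/350 = 22.9%.

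**5. Power at 81.7 per arm.** The article gives neither a standard deviation nor a baseline mean, so the standardised difference has to be solved back from 90 per arm. Assume that 90 gives exactly 80% power:

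- d = (1.960 + 0.842) × √(2/90) = 0.418 by the normal approximation (0.420 by the noncentral t)
- power at 81.7 per arm = Φ(0.418 × √(81.7/2) − 1.960) = Φ(0.709) = 0.761 (0.760 by the noncentral t)

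| Loss | Analysed in total | Per arm | Power |
|---|---|---|---|
| 20% | 280 | 93.3 | 81% |
| 22.9% | 270 | 90.0 | 80% |
| 25% | 262.5 | 87.5 | 79% |
| 30% | 245 | 81.7 | 76% |

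**6. Detectable difference.** With the standard deviation held fixed, the difference detectable with 80% power scales with 1/√n: 20% × √(90/81.7) = 21.0%.

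**The case against.** **The consequence is small and conditional.** Power falls by about 4 points, and only if the full 30% is lost. The Follow-up section plans telephone reminders and a replacement questionnaire, so 30% may be a cautious allowance and not a forecast. The primary analysis, the type I error and the interpretation of the result are unaffected. All of this is true. It limits the weight of the point but does not make the sentence correct, because the plan itself says that 350 allows for 30%.

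**Recruited and randomised may be different counts.** The Consent and Randomisation sections put registration and a first treatment session before randomisation. If the 30% ran from registration, then 386 recruited, 350 randomised and 270 analysed would fit together. This reading fails on the article's own text: the Abstract gives 350 as the number recruited, the Randomisation section randomises those recruited, and no loss before randomisation is stated anywhere.

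**The 76% rests on an assumption.** The 90 per group cannot be rebuilt from the article. If it had been rounded up from, say, 85, power at 81.7 per arm would be Φ(2.802 × √(81.7/85) − 1.960) = 0.78. This stands, and the 76% should carry its assumption, although calling 90 the minimum makes exactly 80% the natural reading. The gap between 350 and 386 does not depend on it.

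**Conclusion.** The concern holds. The 270 analysable participants, the 30% drop-out among those recruited and the 350 to be randomised contradict one another, and nothing else in the article reconciles them. The number that fits 30% loss is 386; 350 fits loss of up to 22.9%. This part is plain arithmetic on the plan's own figures and needs no assumption.

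At 30% loss the primary comparison has about 76% power, and the difference detectable with 80% power is about 21%. These two figures assume that 90 per arm gives exactly 80% power and that losses are spread evenly over the arms. The effect on the trial is modest; the error in the stated justification is certain.

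The finding concerns the primary comparison only. The article states no effect size or power of its own for sham acupuncture against advice and exercise alone, so no stated power is missed there.

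**What to change.** Correct the last sentence of the Sample size calculation section and leave the target at 350. For example:

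> Randomising 350 participants keeps 270 for analysis, and so 80% power for the primary comparison, if no more than about 23% are lost. At 30% loss, about 82 per group would remain and power would be about 76%, taking 90 per group as giving 80%.

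If the authors would rather keep the 30% allowance as the design basis, the number that it requires is 386, and the Abstract would have to agree with it. Restating the coverage of 350 is enough, so this is not a call to enrol more participants.

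The cost is one sentence and a slightly less favourable power statement. Design, recruitment and analysis do not change.

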### Analysis

Collection of data and statistical analysis will be performed blinded to treatment allocation. Analysis will be performed on an intention to treat basis and the primary outcome will also be analysed on a "per protocol basis".

Univariate analysis will be performed using t-tests to analyse numerical data and chi-square tests for categorical data. The clinical and demographic data collected at baseline will be inspected and if there are any important differences between the trial groups, these factors will be used as covariates. These analyses will be performed using ANOVA and logistic regression as appropriate.

The analysis of the secondary outcomes will be exploratory. A univariate analysis with respect to the different treatment will be performed for the WOMAC pain sub-scale at 6-weeks and 12-months and for the WOMAC functioning sub-scale at 6-weeks, 6- and 12-months. The global outcome assessment with be analysed both as an ordinal and a dichotomous variable (categories 1–3 defined as "success"). Moreover, area under the curve slopes will be calculated for each treatment group over the whole treatment period and compared.

Statistical significance will be set at the 5% level (two-tailed). Statistical analysis will be performed using Stata 7.0. The trial will be monitored by an independent Data Monitoring and Ethics Committee. No interim analysis of the primary or secondary outcomes will be undertaken during the trial period.

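### The planned 6-month t-test leaves the baseline and 6-week WOMAC pain scores unused although 30% drop-out is expected; a pre-specified repeated-measures model would do better at little cost

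*Protocol article*

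**What the plan says.** Under Sample size calculation, "The primary outcome measure for this trial is the Western Ontario and McMaster Universities Osteoarthritis Index (WOMAC) pain sub-scale", and the trial is sized on a "20% difference in the WOMAC pain sub-scale between true acupuncture and advice and exercise alone at 6 months", with 90 per group for 80% power at two-sided 5%. Three groups make 270, and the total becomes 350, "Allowing for a 30% drop out rate in those recruited to the trial".

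Under Analysis, "Analysis will be performed on an intention to treat basis", with a per-protocol analysis of the primary outcome alongside. For the method, "Univariate analysis will be performed using t-tests to analyse numerical data and chi-square tests for categorical data". Baseline data are to be inspected, and factors showing important group differences become covariates: "These analyses will be performed using ANOVA and logistic regression as appropriate". For the exploratory secondary outcomes, "A univariate analysis with respect to the different treatment will be performed for the WOMAC pain sub-scale at 6-weeks and 12-months", and an area-under-the-curve comparison over the whole period is also planned.

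Under Baseline measures, the baseline questionnaire supplies the starting values of the outcomes. Under Follow-up, non-responders are telephoned up to twice and then sent a replacement questionnaire with a reminder letter. The article does not say how a missing 6-month score is treated in the analysis.

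**The concern.** A t-test at one time point needs a score at that time point. Someone who returned the baseline and 6-week questionnaires but not the 6-month one contributes nothing to it unless a value is imputed first. With 30% loss allowed for, that could be a sizeable part of the primary comparison.

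Two things are at stake. The first is the assumption about missing data. Comparing available 6-month scores relies on loss not distorting the arms differently. A likelihood model that also uses baseline and 6-week scores needs a weaker assumption, because loss may depend on those observed scores. Differential loss is at least conceivable here: outcomes come from postal self-report, participants have never had acupuncture, and those allocated to advice and exercise alone know they are not receiving it.

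The second is precision. Baseline WOMAC pain probably predicts the 6-month score, yet it enters the analysis only if the arms happen to look different. That makes the primary model depend on an inspection of the data and gives up a gain available whether or not the arms are balanced.

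**Working it through.** **Inputs from the article:** 90 per group, 80% power, two-sided 5%; 3 × 90 = 270; 30% drop-out; 350 randomised 1:1:1. No SD is given.

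**The plan's own figures.** The 90 per group cannot be reproduced without an SD, but it can be solved backwards: d = (1.960 + 0.842) × √(2/90) = 0.418 SD. The total of 350 matches 270 × 1.30 = 351. Dividing instead, 270 / 0.70 = 386. That is a separate sample-size point, used here only to see what remains after the planned loss.

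**Numbers left.** 350 × 0.70 = 245, or 81.7 per arm, so 105 are lost over three arms. The primary contrast has two arms: 350 × 2/3 = 233 randomised, of whom 0.30 × 233 = 70 are lost.

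**Power of an unadjusted comparison at the planned loss.** Power = Φ(d × √(n/2) − 1.960). With d = 0.418 and n = 81.7, d × √(n/2) = 2.669, so power = Φ(0.709) = 76%.

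**Power with baseline as covariate.** The residual SD falls by √(1 − r²), where r is the correlation between baseline and 6-month WOMAC pain. The article gives no r, so a range is assumed:

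- r = 0.3: 2.669 / √0.91 = 2.798; Φ(0.838) = 80%.
- r = 0.5: 2.669 / √0.75 = 3.082; Φ(1.122) = 87%.

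This gain comes from the baseline covariate alone. Any further gain from participants with a 6-week but no 6-month score is not counted.

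**Possible bias of an available-case comparison.** Let p be the fraction missing in an arm and g the mean of the missing minus the mean of the observed, in SD. Subscript C is advice and exercise alone; A is true acupuncture. The full-arm difference minus the observed difference (C minus A) is p_C × g_C − p_A × g_A. Every p and g split by arm is an assumption.

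| Scenario | Calculation | Shift (SD) | Share of 0.418 |
|---|---|---|---|
| Equal loss, equal gap | 0.30 × 0.4 − 0.30 × 0.4 | 0 | 0% |
| 35% v 25% loss, same gap of 0.5 | 0.35 × 0.5 − 0.25 × 0.5 | 0.05 | 12% |
| 30% each, gap of 0.4 in one arm only | 0.30 × 0.4 | 0.12 | 29% |
| 35% v 25% loss, gaps of 0.5 in opposite directions | 0.35 × 0.5 + 0.25 × 0.5 | 0.30 | 72% |

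The table shows how far the answer depends on the assumption. The last row is one severe scenario and not a bound.

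**The case against.** The article never says that only responders are analysed, and never calls the primary analysis complete-case. A t-test or ANOVA can follow imputation, a drop-out allowance does not define the analysis set, and missing-data handling is commonly left to an analysis plan that is not shown. All of this stands. A reader might infer that the plan breaks its own intention-to-treat commitment. The text does not support that: intention to treat is set against per protocol in the same sentence, so it most naturally means analysis by allocated arm, which a t-test respects. The model proposed below also omits people with no follow-up score.

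A reader might also infer that the primary result will be biased by some stated amount. That fails too. The gaps and loss rates by arm are assumed, the formula gives zero when outcome-related loss is equal across arms, and the article plans active chasing of non-responders. Nor would a mixed model necessarily remove the severe scenario: if people leave because of recovery or dissatisfaction that their earlier scores do not reflect, it is biased as well.

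Finally, the plan is not confined to separate t-tests. It allows covariate-adjusted analyses and an area-under-the-curve comparison. The first depends on observed imbalance, however, and the second is not the primary 6-month contrast. Neither secures use of the earlier WOMAC pain scores in the primary result. The choice of t-test with conditional covariates is stated in the article, and that is what the point rests on.

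**Conclusion.** The point holds as a weakness in the stated method. It is neither a contradiction nor a demonstrated bias. Unless imputation is specified elsewhere, the primary t-test uses only those with a 6-month score, which at the planned loss leaves out about 70 of 233 in the two-arm contrast.

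The best-supported cost is precision: about 76% power at the planned loss, against about 80% to 87% with baseline WOMAC pain as a covariate. This rests on the back-solved difference of 0.418 SD, an even 30% loss and an assumed correlation of 0.3 to 0.5. The scenarios of 0.05 to 0.30 SD show why a weaker missing-data assumption is worth having; they do not estimate what will happen, and zero is equally compatible with the article. The change should be made, because it is cheap and relies on data already planned.

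**What to change.** Make the primary analysis a pre-specified linear mixed model for WOMAC pain at 6 weeks, 6 months and 12 months, with arm by time, baseline WOMAC pain and centre. Include every participant with at least one follow-up score, in the arm to which they were randomised. Name the 6-month contrast of true acupuncture plus advice and exercise against advice and exercise alone as the primary result. Baseline WOMAC pain enters whether or not the arms look balanced.

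Keep the 6-month t-test as a supporting analysis and state who is in it. Add one sensitivity analysis that shifts the missing 6-month scores by different amounts in the two arms, because the model still assumes that data are missing at random.

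The cost is revised analysis wording and a little more programming. The downside is reliance on the missing-at-random assumption, which the shift analysis examines. No new data are needed.

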### Randomisation

Randomisation will take place after this initial physiotherapy session. The treating physiotherapist will telephone the Research Centre at Keele University, during normal working hours. This methodology ensures that the initial physiotherapy assessment and advice and exercise package provided is performed blind to subsequent treatment allocation. The specific trial interventions will commence during the participant's second treatment visit. During the randomisation telephone call the physiotherapist will be asked to identify the selected acupuncture sites to check that the participant has received their first pre-randomisation treatment session. The physiotherapists will also be asked questions about their own expectations of the individual participant's likely clinical outcome and their beliefs about which treatment they would like the participant to receive. Participants recruited to the trial will then be randomised to one of the three trial interventions in a 1:1:1 ratio based on their unique trial number. Computerised third-party randomisation will be performed using random permuted blocks of 12 (blocked by treatment centre).

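### Covariates enter only if baseline differences look important, so baseline WOMAC pain has no pre-specified role in the primary 6-month comparison

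*Protocol article*

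**What the plan says.** All places are in the Methods of the protocol article.

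- **Primary outcome (Sample size calculation):** "The primary outcome measure for this trial is the Western Ontario and McMaster Universities Osteoarthritis Index (WOMAC) pain sub-scale". The target comparison is true acupuncture against advice and exercise alone: "We have defined overall success as a 20% difference in the WOMAC pain sub-scale between true acupuncture and advice and exercise alone at 6 months".
- **Unadjusted test (Analysis):** "Univariate analysis will be performed using t-tests to analyse numerical data". The text does not say whether the t-test is on the 6-month score or on change from baseline.
- **Covariate rule (Analysis):** baseline clinical and demographic data are inspected, and "if there are any important differences between the trial groups, these factors will be used as covariates". The adjusted analyses are ANOVA or logistic regression. No threshold for importance is given and no covariate is named in advance.
- **Baseline data (Baseline measures):** of the baseline questionnaire items, "These variables will be used to describe the study sample and as baseline measures of outcomes".

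**The concern.** In a randomised trial, baseline differences between arms arise by chance. How large they turn out to be is a poor guide to which covariates belong in the model. What matters is how strongly a covariate predicts the outcome, and that can be judged before any data are seen. A baseline measurement of the outcome itself is the natural candidate, and it is already collected here.

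Under the stated rule, baseline WOMAC pain enters the model only if the arms happen to differ on it. In most trials they will not differ noticeably, so the precision available from adjustment is not used. Because importance is undefined, two analysts reading the same baseline table could also settle on different models for the primary outcome.

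**Working it through.** **Inputs from the documents.** "a minimum of 90 participants is needed in each group", "with 80% power and at a 5% significance level (two-tailed"); patients are "randomised to one of the three trial interventions in a 1:1:1 ratio". The text gives no mean or SD, and does not say what the 20% is relative to.

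**Assumed.** The correlation r between baseline and 6-month WOMAC pain is not given. I show 0.3 to 0.6, and 0.7 where it was simulated.

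**Step 1: the plan's own figure.** Without an SD, 90 per group cannot be reproduced directly, so I inverted it (normal approximation, two-sided 5%, equal arms):

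d = (1.960 + 0.842) × √(2/90) = 2.802 × 0.149 = 0.418

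If the 20% is relative to a mean, this corresponds to an SD of 0.20/0.418, about 48% of that mean. By construction, a t-test on the 6-month score with 90 per arm then has 80% power.

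**Step 2: ANCOVA at 90 per arm.** Adjusting for baseline multiplies the residual SD by √(1 − r²), so power = Φ(2.802/√(1 − r²) − 1.960).

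**Step 3: change score at 90 per arm.** This alternative is not excluded by the text. The SD is multiplied by √(2(1 − r)), so power = Φ(2.802/√(2(1 − r)) − 1.960).

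| r | √(1 − r²) | ANCOVA power | √(2(1 − r)) | Change-score power | t-test on 6-month score |
|---|---|---|---|---|---|
| 0.3 | 0.954 | 83.6% | 1.183 | 65.8% | 80% |
| 0.4 | 0.917 | 86.4% | 1.095 | 72.5% | 80% |
| 0.5 | 0.866 | 89.9% | 1.000 | 80.0% | 80% |
| 0.6 | 0.800 | 93.8% | 0.894 | 88.0% | 80% |

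ANCOVA has the highest power in every row. Its lead over the change score narrows from about 18 points at r = 0.3 to about 6 at r = 0.6.

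**Step 4: the imbalance rule itself.** I simulated 100,000 trials per scenario with 90 per arm. The article gives no trigger, so importance was represented by a baseline t-test with p below a cut-off. The t-test was on the 6-month score.

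| Power | r = 0.3 | r = 0.5 | r = 0.7 |
|---|---|---|---|
| t-test always | 80% | 80% | 79% |
| Adjust only if baseline p < 0.05 | 80% | 81% | 81% |
| Adjust only if baseline p < 0.20 | 81% | 83% | 86% |
| ANCOVA always | 83% | 89% | 97% |

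At the 0.05 trigger the rule recovers little of the gain. A looser trigger recovers more, but still falls short of always adjusting.

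**Step 5: type I error and agreement, at r = 0.3 / 0.5 / 0.7.**
- Rule applied mechanically at p < 0.05: 4.8% / 4.4% / 3.5%, which is slightly conservative.
- Whichever of the two results is significant may be reported: 6.3% / 7.4% / 8.2%.
- Under the alternative, the t-test and ANCOVA disagree on significance in 7% / 13% / 19% of trials.

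**The case against.** Four points on the other side have force.

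1. **Baseline pain is not thrown away.** A reader might infer that the plan discards it. The text does not support that: the score enters if it is judged imbalanced, and a change-score t-test is not ruled out. What can be said is that it has no fixed role. If a change score was meant, the gain from ANCOVA at r = 0.6 is about 6 points rather than 14.
2. **The unadjusted t-test is not named as the primary analysis.** The article lists univariate tests and then covariate-adjusted ones without ranking them. Ranking them may be left to an analysis plan that is not shown, so its absence is not counted here. The imbalance trigger is different, because the article states it outright.
3. **The rule does not make inference invalid.** A reader might infer a data-driven primary result with inflated error. But the rule looks at baseline data, not outcomes, and the article says that analysis is blinded to allocation. Applied mechanically, it keeps type I error at or below 5%. Inflation needs a free choice between the two results. The undefined trigger leaves room for that, but the article does not say it will happen.
4. **The shortfall after drop-out is a separate issue.** With 350 randomised and 30% lost, about 82 per arm remain (350/3 × 0.7 = 81.7), and the t-test then has about 76% power. That follows from the drop-out arithmetic, not from the choice of analysis. At the planned 90 per arm the t-test meets its 80% target.

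None of these gives a reason to let observed imbalance decide whether the baseline score is used. Blinding limits bias in the choice, but it neither defines the trigger nor recovers precision.

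**Conclusion.** The concern holds as a loss of efficiency and an imprecise covariate rule, not as invalid inference. The plan lets chance imbalance, judged by an undefined criterion, decide whether baseline WOMAC pain enters the primary comparison.

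At 90 evaluable per arm, pre-specified ANCOVA raises power over a t-test on the 6-month score by about 4 points (r = 0.3), 6 (r = 0.4), 10 (r = 0.5) or 14 (r = 0.6). The simulated rule with a 0.05 trigger stays at about 80 to 81%.

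These sizes rest on an effect of about 0.42 back-solved from the plan's own sample size, on assumed correlations, and on the normal approximation for the formula results. The direction does not depend on the exact values: for any appreciable correlation, ANCOVA is more precise than either t-test.

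**What to change.** In the Analysis section, state that the primary analysis is a linear model (ANCOVA) of 6-month WOMAC pain on treatment, with baseline WOMAC pain as a pre-specified covariate, reported as an adjusted mean difference with a 95% confidence interval. Delete the sentence that adds covariates when baseline differences look important. Keep the unadjusted t-test as a sensitivity analysis.

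Use the same approach, with each measure's own baseline, for WOMAC pain at 6 weeks and 12 months and for WOMAC function at all three time points. The linear model does not carry over to the global assessment, which is analysed as ordinal and dichotomous.

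The cost is a change of wording. The baseline measures are already collected, and recruitment, treatment and follow-up are unaffected. The article plans no interim analysis of outcomes, so the change can be made before outcome data are examined.
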